#### Blinding

The nature of the interventions precludes full blinding, but a number of key assessments will be blinded to minimise performance bias. By necessity, treating clinicians will be aware of group allocation throughout the duration of the participants’ care until the point of healing. Clinical judgements of re-epithelialisation, therefore, will not be blinded, but the use of 3D photographs will allow for a later review by a panel of blinded assessors. These assessors will not be provided any details pertaining to the participants’ management. If there any discrepancies, the blinded measures (or the majority thereof) will supersede those taken by clinicians.

Skin and scar assessments performed at 3- and 6-month follow-up appointments will also be blinded, as the clinical evaluators will have no knowledge of participants’ acute care. To reduce the risk of performance bias further, ultrasound images taken at these follow-ups will be reviewed by blinded assessors, who will measure scar and wound site thicknesses.

#### Primary outcome measure

##### Time to re-epithelialisation

The primary outcome will be time to full re-epithelialisation, as measured by the number of days from the injury to 95% re-epithelialisation of the burn wound. Percentage re-epithelialisation will be assessed at every clinical visit using multiple methods. A treating consultant will first perform an examination and record their assessment. Digital 3D photographs will then be taken of the burn using the 3DLife Viz II (Quantificare, Valbonne, France) and the D400 3D (Intel, Santa Clara, US) cameras. These photographs will be analysed using the software programs DermaPix (Quantificare, Valbonne, France) and 3D WoundCare (GPC, Swansea, UK), respectively, and undergo blinded review by a panel of three burns clinicians.

#### Secondary outcome measures

##### Pain

Pain intensity will be assessed at various time points throughout the participants’ management. At their first clinical visit, baseline pain measures will be recorded immediately prior to and following dressing applications. The same measures will be repeated before and after dressing changes at every subsequent clinical visit until the burn is considered fully re-epithelialised.

A variety of measures and age-dependent scales will be utilised to assess pain. Nurses will provide an observational rating using the Face, Legs, Activity, Cry, Consolability (FLACC) scale, which is accepted as a valid and reliable tool for assessing trauma-related pain behaviours in preverbal children [99, 100]. Children aged 4 to 7 years will be asked to self-report their pain using the Revised Faces Pain Scale (FPS-R) and those aged 8 years and older will self-report their pain using a numerical rating scale (NRS).

There is a large volume of literature demonstrating the validity and reliability of the FPS-R in children as young as 4 years old [101, 102]. For children aged 8 years and older, both the NRS and a visual analogue scale are well-validated tools [103, 104], but several comparison studies have expressed a preference for the NRS, which is associated with higher levels of responsivity, adherence and ease of use in the assessment of pain intensity among adults [105, 106]. Furthermore, the NRS allows for greater consistency throughout the full duration of the trial, as the two skin/scar assessment scales employed at the 3- and 6-month follow-ups both include numerical pain ratings.

To supplement the above pain ratings, investigators will additionally document the type and dosage of all analgesic medications administered to patients by health professionals or parents during the days on which they present to the clinic.

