##### Recruitment

All patients presenting to the ED or burns OPD with acute burns will be consecutively assessed for eligibility until the completion of recruitment. Nursing and surgical staff will identify eligible patients. In the ED, clinicians will first request permission from caregivers before inviting an investigator to approach them. If presenting to the burns OPD, potential participants will be approached only if they indicate a willingness to take part in research on an initial intake questionnaire.

An investigator will seek informed caregiver consent and child assent (for children 6 years and above) following the provision of verbal and written participant information. Once consent has been obtained, the patient will be randomised to one of the two treatment arms.

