All interventions will be carried out by burns clinicians with extensive experience in the application of dressings and NPWT. Following their initial presentation, participants will return to the OPD 3 to 5 days later for a change of dressings and, for those in the intervention group, a replacement of their NPWT system. To alleviate any additional pain from the removal of the adhesive drape, the clinicians replacing the NPWT apparatus will apply Niltac™ (ConvaTec, Greenlane, NZ), a silicone-based spray that can effectively dissolve the film and ease extraction. Participants will continue to present to the burns clinic every 3 to 5 days for dressing and NPWT changes until the wound is fully re-epithelialised or until grafting is required.

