##### Pruritus

Itch severity will be measured concurrently with pain intensity. Unlike pain, emotional health, physical function and mobility, pruritus is one of the few domains in which parental and child perceptions significantly differ among paediatric burns patients [107]. As such, self-reports will be sought wherever possible. The only self-reporting itch scale that has been validated in children is the Itch Man Scale, which is recommended in children over the age of 5 years [108].

For patients too young to comprehend and cooperate with self-reporting scales, caregivers will be asked to perform an observational assessment using the Toronto Paediatric Itch Scale. This tool, which rates pruritus behaviours on a scale of 0 (absence of itch) to 3 (severe itch with significant disruption), has been found to assess itch severity in children aged 5 years or less with reasonable validity and reliability [109].

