##### Grafting

With the inclusion of deep dermal partial-thickness and full-thickness burns in the eligibility criteria, it is anticipated that some participants will ultimately require skin grafting to achieve wound closure. All surgical procedures will be documented by investigators, but data collection will be discontinued for these patients at the point of grafting. Any data obtained prior to grafting will be included in the final analysis following an intention-to-treat methodology.

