#### Data analysis

Conventional descriptive statistics will be used to describe the characteristics of the sample.

The potential effect of time to treatment, burn depth, burn TBSA, mechanism of injury, anatomical location of the burn and skin type will also be tested against primary and secondary measures in univariate analyses. Variables with *p*
< 0.1 will be included as covariates in the primary and secondary analyses. Sensitivity analyses will also be conducted without adjustment for covariates.

Generalised linear (mixed) models will be prepared to examine primary and secondary outcomes across time and between groups, with patients as random effect where analyses include repeated measures within a patient. If mixed models do not converge with patient as a random effect, robust variance estimates for cluster-correlated data will be used [128]. For outcomes with repeated measures, the fixed effects of time, group and interaction time by group will be tested. Data will be analysed as intention-to-treat (primary analysis) and on a per protocol basis (sensitivity analysis) if deviations from the protocol occur. Missing data will be handled using multiple imputation where appropriate. Significance will be set at 0.05. Statistical analyses will be performed using Stata (StataCorp LLC College Station, TX:) or SPSS (IBM Corp, Armonk, NY, USA).

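### A score taken after the allocated dressing is labelled baseline, the pre-dressing pain and itch score is not among the listed covariates, and clinic scores stop at healing

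*Protocol article*

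**What the plan says.** - **Pain, first visit:** "baseline pain measures will be recorded immediately prior to and following dressing applications".
- **Pain, later visits:** scores are repeated "before and after dressing changes at every subsequent clinical visit until the burn is considered fully re-epithelialised".
- **Pruritus:** "Itch severity will be measured concurrently with pain intensity", so whatever holds for the timing of clinic pain holds for itch.
- **Recruitment:** "Once consent has been obtained, the patient will be randomised to one of the two treatment arms".
- **Interventions:** "participants will return to the OPD 3 to 5 days later for a change of dressings and, for those in the intervention group, a replacement". Negative pressure is therefore already in place after the first visit.
- **Grafting:** "data collection will be discontinued for these patients at the point of grafting".
- **Data analysis:** "For outcomes with repeated measures, the fixed effects of time, group and interaction time by group will be tested". Six candidate covariates are named: time to treatment, burn depth, TBSA, mechanism, anatomical location and skin type. The pain or itch score before the first dressing is not one of them. The section does not say whether that score is an outcome row, or which of the three tested terms is the treatment effect.
- **Pain and itch at home:** surveys go out 24–48 h after each dressing application or change.

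**The concern.** Pain is one of the three effects that the Hypothesis and objectives section sets out to measure. Three features of the text bear on how well that can be done.

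1. The label baseline covers a score taken after randomisation and after the allocated dressing is on. An analyst who used it as baseline, or averaged it with the pre-dressing score, would subtract any immediate effect of application from the comparison.
2. The one true pre-treatment score is collected, yet it is missing from a covariate list that is otherwise spelled out. The usual gain in precision from adjusting for it is then not planned, and the score could end up as one more time point in the outcome.
3. The clinic series ends at the event that NPWT is expected to bring forward. At later visits each arm is represented by its slower healers, and the two arms lose children at different rates.

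**Working it through.** **The plan's own figure.** Two-sample t-test, difference 3.4 days, SD 5.4, 5% two-sided (sidedness assumed), 80% power: 40.6, so 41 per arm. 41 / 0.80 = 51.25, so 52 per arm and 104 in total, as stated. Nothing below depends on this or changes it.

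**Order of events at the first visit.** Consent, randomisation, pre-dressing score, allocated dressing (with NPWT in one arm), post-application score. The last is post-randomisation and post-treatment.

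**Effect of including a pre-treatment row.** Take K scores, one of them pre-treatment, and a constant effect on the others. A group effect averaged over all K keeps (K − 1)/K of it: 2/3 = 67% at K = 3 and 5/6 = 83% at K = 6. K = 6 is what three visits give with a score before and after each dressing.

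**Efficiency of three analyses.** The documents give no SD, effect or correlation for pain. Assumed: effect 1.2 points, SD 2.5 (so 0.48 SD), correlation r = 0.4 between any two scores, all scores observed, 42 per arm (52 × 0.8 = 41.6). With m = K − 1 post-treatment scores and variances in SD² units:

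- group main effect over all K: V = (1 + (K − 1)r)/K, effect 0.48(K − 1)/K
- mean of the post scores: Vpost = (1 + (m − 1)r)/m
- time-by-group contrast (mean post minus pre): V = Vpost + 1 − 2r, effect 0.48
- baseline as covariate: V = Vpost − r², effect 0.48

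SE = √(2V/42); power is from the t distribution with 82 df.

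| | K = 3: V | effect | power | K = 6: V | effect | power |
|---|---|---|---|---|---|---|
| Group main effect, pre row included | 0.60 | 0.32 | about 47% | 0.50 | 0.40 | 73% |
| Time-by-group contrast | 0.90 | 0.48 | 63% | 0.72 | 0.48 | 73% |
| Baseline as covariate | 0.54 | 0.48 | 84% | 0.36 | 0.48 | 95% |

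A single post-treatment score adjusted for baseline has V = 1 − 0.16 = 0.84 and power 66%.

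**Who is still being scored.** Healing means are 12.4 days (SD 5.4, Sample size section) and 12.4 − 3.4 = 9.0. The lognormal shape is an assumption, as is the NPWT SD: 5.4 (equal SD) down to 3.9 (equal coefficient of variation, 9.0 × 5.4/12.4). With σ² = ln(1 + (SD/mean)²) and μ = ln(mean) − σ²/2:

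- control: σ = 0.417, μ = 2.431
- NPWT, SD 5.4: σ = 0.555, μ = 2.044
- NPWT, SD 3.9: σ = 0.415, μ = 2.111

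Share unhealed = 1 − Φ((ln t − μ)/σ):

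| Day from injury | Control | NPWT |
|---|---|---|
| 4 | 99% | 88–96% |
| 9 | 71% | 39–42% |
| 13 | 37% | 14–17% |

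A normal shape with SD 5.4 in both arms gives 74% v 50% at day 9 and 46% v 23% at day 13.

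**What selection could do to pain.** A simulation used no direct effect of NPWT on pain, SD 5.4 in both arms, and an assumed positive correlation of 0.3 to 0.7 between pain and healing time. Among children still unhealed, NPWT looks worse by 0.06–0.14 SD at day 4 and by 0.14–0.34 SD at days 8 and 12. A negative correlation would reverse the sign.

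**The case against.** A reader might infer that the pain analysis as written is diluted by a third and underpowered. The documents do not support that. The Data analysis section never says that the pre-dressing score is an outcome row or that the group main effect is the estimate, and a statistical analysis plan that is not shown could settle both. It also names the time-by-group term, which measures change from the pre-treatment score and is not diluted. The loss of one third arises only with three scores; before-and-after scoring at three visits gives six, and the loss is then one sixth.

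The home scores, which best match the hypothesis about pain and itch between dressing changes, all come after treatment starts, so they contain no pre-treatment row to dilute anything.

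Baseline may also simply mean the baseline visit, a term that the Ease of management section uses. No text says that the post-application score will serve as a covariate.

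These objections remove the claim that the effect is necessarily understated. They do not remove the ambiguous label, the omission of a collected prognostic score from an explicit covariate list, or the stopping of clinic scores at healing, all of which are stated in the article.

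A second tempting inference is that later visits are biased against NPWT. That needs a positive correlation between pain and healing time, and the documents give none.

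Finally, restricting all inference to one early score would be costly if later scores are well observed: 66% power, against 84–95% when all post-treatment scores are used with baseline adjustment. Later visits should therefore not be reduced to description.

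**Conclusion.** The point holds in a limited form. The label baseline covers a post-treatment score, for pain and, through shared timing, for itch. The pre-dressing score is not among the candidate covariates, and the term that carries the treatment effect is not identified. Dilution to 67–83% is conditional on one reading of the model. The efficiency gain from baseline adjustment over the interaction contrast (63% to 84%, or 73% to 95%) does not depend on that reading, but it rests on an assumed effect, SD and correlation and on complete scores.

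Unequal loss of children at healing follows from the plan's own means, given an assumed distribution: 71% v 39–42% unhealed at day 9 and 37% v 14–17% at day 13. The size and direction of any bias in pain are unknown. The primary outcome and the sample size of 104 are untouched. It is worth changing because the remedy is wording only and pain is a stated target of the trial.

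**What to change.** State in the analysis section:

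1. Baseline pain and baseline itch are the first-visit pre-dressing scores only.
2. That score enters the clinic and home pain and itch models as a covariate, with age stratum (instrument), and is not an outcome row. For itch, the scale changes at about 5 years, inside the 4-to-7 stratum, so use an indicator for the scale.
3. The first-visit post-application score is an outcome.
4. The main contrast is at one named early time when most children are still unhealed: the first home survey or the first dressing change. The home survey fits the between-change hypothesis more closely and comes earlier.
5. Later visits stay in a supporting baseline-adjusted repeated-measures model, interpreted as conditional on being unhealed, with a statement of how scores after healing or grafting are treated.

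Cost: analysis wording, with no new data and no change to recruitment, which stood at 103 when the article was written. The downside is that later visits carry less weight in the main pain test. The wording should be fixed before outcome data are examined by arm.

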##### Pruritus

Itch severity will be measured concurrently with pain intensity. Unlike pain, emotional health, physical function and mobility, pruritus is one of the few domains in which parental and child perceptions significantly differ among paediatric burns patients [107]. As such, self-reports will be sought wherever possible. The only self-reporting itch scale that has been validated in children is the Itch Man Scale, which is recommended in children over the age of 5 years [108].

For patients too young to comprehend and cooperate with self-reporting scales, caregivers will be asked to perform an observational assessment using the Toronto Paediatric Itch Scale. This tool, which rates pruritus behaviours on a scale of 0 (absence of itch) to 3 (severe itch with significant disruption), has been found to assess itch severity in children aged 5 years or less with reasonable validity and reliability [109].

##### Pain and itch at home

Due to the multi-day durations of NPWT and silver-impregnated dressing treatments, measurements of pain and pruritus will be undertaken not only in the clinic but also at home, where most of the patients’ time undergoing their respective therapies will be spent. Caregivers will be contacted via text messages 24–48 h after every dressing application or change with a link to an online survey generated on REDCap. The survey will be automatically modified according to patient age to provide the appropriate pain and itch scales.

Retrospective reporting and recall bias are frequent risks associated with more traditional take-home questionnaires, with major implications for the validity of the outcomes they provide. [110–112] Online data collection via SMS notifications offers a valid alternative capable of prompting real-time assessments with a very high response rate and reduced management burden [113]. Moreover, any retrospective reports can be easily identified by their time stamps and evaluated accordingly.

If caregivers fail to complete the survey following the first message, they will be sent reminders every 24 h until they either submit their responses or attend their next clinical appointment. For those not in possession of a mobile phone or not agreeable to receiving research-related text messages, investigators will offer to send the surveys to their preferred email account, call their landline to collect the data verbally or, as a last resort, supply paper questionnaires.

##### Wound depth and progression

In addition to the treating consultant’s clinical assessments of burn depth and size, laser Doppler imaging (LDI) will be employed to help evaluate the extent of wound progression within burns. LDI measures blood perfusion, rather than directly assessing wound depth, but it is still widely considered to be a highly effective and accurate diagnostic tool for burn depth assessments [114]. As progression of wound depth and size is known to take place within the first 4 to 5 days post-burn [47, 115], LDI will be performed only at patients’ initial presentation and their first follow-up 3 to 5 days later. For each scan, investigators will record flux maximum, minimum, mean and standard deviation.

##### Treatment satisfaction

Clinicians in the burns OPD have observed anecdotally that older children and adolescents tend to be less tolerant of NPWT than younger patients. To evaluate quantitatively attitudes toward NPWT and how they vary with age, treatment satisfaction will be assessed at every clinical visit via the use of an 11-point NRS (0 = not at all satisfied; 10 = extremely satisfied). As with the NRS for pain, caregivers will provide an observational measure for children up to the age of 7 years, whilst those 8 years and older will self-report. Caregivers of all children will be asked to rate their own satisfaction with the treatment as well.

##### Physical function

Participants’ physical function while undergoing treatment will be assessed by patients and/or caregivers at every clinical visit, also via an 11-point NRS (0 = not at all easy to move; 10 = extremely easy to move).

##### Ease of management

The treating nurse will be surveyed on their views of the interventions after each baseline visit and change of dressings. They will specifically assess ease of removal and application, using another 11-point NRS (0 = not at all easy to remove/apply; 10 = extremely easy to remove/apply).

##### Scar and skin assessments

At 3 and 6 months following the burn injury, face-to-face follow-ups will be completed with all participants to conduct skin or scar reviews in conjunction with occupational therapy.

Ultrasound will be used to measure the thickness of the healed wound or scar. Scans will be taken centrally at each site of interest with the BT12 Venue 40 MSK ultrasound machine (General Electric, Little Chalfont, UK). The investigators will record and calculate an average of three thickness measurements within the central area at the time of the scan. These measurements will be compared to those taken from scans of healthy unburned skin contralateral to the site of the burn. Digital copies of the scans will be saved for later evaluations by blinded reviewers.

An objective quantification of the lightness, erythema, and pigmentation of the healed wound or scar will be obtained using the DSM II ColorMeter (Cortex Technology, Hadsund, Denmark). In paediatric studies, the device has exhibited high levels of inter-rater reliability [116], including among children with burn scars [117]. At each follow-up, two measurements will be taken of both the site of interest and a region of healthy skin for comparison.

The Patient and Observer Scar Assessment Scale (POSAS) will also be completed with the child (if over the age of 8 years) and caregiver. As a scar severity evaluation tool, the POSAS is both reliable and feasible [118–120], with an observer scale that shows adequate reliability in the assessment of scar appearance in children [117]. Another instrument, the Brisbane Burn Scar Impact Profile (BBSIP), will be used to measure scar patients’ physical and sensory symptoms as well as their health-related quality of life. Developed primarily for children, the BBSIP has undergone preliminary validation in paediatric patients at the participating burns centre [121].

##### Resource use and costs

Resource usage (and costs) for the care of each patient will be recorded from the perspective of the health service consistent with prior studies in the field [122, 123]. This will include details of the trial interventions, including the number of clinical visits, the duration of each visit, the dosages of analgesic medications prescribed, the quantity of dressings and NPWT products used, and associated labour time. Resource use will be costed at market rates (e.g., clinician time attributable to each participant will be costed based on relevant state-award salary rates). For patients requiring subsequent scar management, details of scar management (including scar interventions and associated clinician labour time) will also be recorded for each patient for the duration of the trial.

